#### Behavioural and health-related outcomes

In addition to acceptability and feasibility, we will assess the following outcome measures in all participants before randomisation and 13 weeks after randomisation: body mass, stature, waist circumference, blood pressure, resting heart rate, cardiorespiratory fitness (ventilatory threshold and peak oxygen uptake), disease status and relapse (CDAI), intestinal inflammation (faecal calprotectin) and blood markers of inflammation* (T lymphocyte subsets [Th1/Th2/Th17] and various cytokines including IL-6, IL-10, TNF-α and C-reactive protein [via 2 × 1-mL blood samples drawn from non-fasted participants at each time point]). Relapse will be defined as an increase in CDAI score of at least 100 points, to a level greater than 150 [19]. Questionnaires will also be administered before and 13 and 26 weeks after randomisation, including the Inflammatory Bowel Disease Quality of Life Questionnaire (IBDQ) [20], EuroQol EQ-5D-5L [21], IBD Fatigue Scale [22], Hospital and Anxiety Depression Scale (HADS) [23] and International Physical Activity Questionnaire (IPAQ)—Short Form [24].

*NOTE: The blood markers of inflammation will also be assessed after 6 weeks of exercise training in the participants in the *two exercise groups only*. Here, venous blood will be collected at the start of the first session of the 7th week of exercise training (i.e. before commencing the 19th exercise session). This additional blood assessment has been included to provide an indication of the time course of changes in circulating inflammatory markers with chronic exercise training.

The assessment of cardiorespiratory fitness will be achieved by measuring ventilatory threshold and peak oxygen uptake. Participants will undergo cardiopulmonary exercise testing using an incremental protocol on an electronically braked cycle ergometer (Lode, Corival, The Netherlands). After 2 min of unloaded cycling, the intensity of exercise will be increased by 15–25 W min^−1^. The target cadence will be 60–80 rev min^−1^. Participants will be encouraged to continue cycling to volitional exhaustion. Heart rate monitoring will be performed continuously (Polar, S610i, Finland). Rating of perceived exertion (RPE; Borg 6–20 scale [14]) will be recorded at the end of every minute. The volume of oxygen consumed during exercise was calculated from minute ventilation and measured using a pneumotachometer and simultaneous breath-by-breath analysis of expired gas fractions (Cosmed, K5, Italy). Gas analysers and flow probes will be calibrated before each test. Oxygen consumption will be expressed relative to body mass (mL∙kg^−1^∙min^−1^). Ventilatory threshold will be determined by an independent exercise physiologist blinded to group allocation using the v-slope and ventilatory equivalents methods [25]. Peak oxygen uptake will be calculated as the highest consecutive 20-s period of oxygen uptake data in the last minute before volitional exhaustion. For an exercise test to be considered valid, at least two of the following criteria must be satisfied: respiratory exchange ratio ≥1.1, RPE ≥17, heart rate ≥95% age-predicted maximum (220 minus age), post-exercise blood lactate ≥6.0 mM.

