### Interventions

#### High-intensity interval training (HIIT)

Participants allocated to the HIIT group will be invited to complete three sessions of HIIT each week for 12 consecutive weeks. It is anticipated that most sessions will be completed within normal office hours (i.e. 0900 to 1700) on Monday, Wednesday and Friday each week; however, early morning, evening and weekend sessions will be offered to facilitate attendance of participants who cannot attend on these days or times. The exercise will be performed on a calibrated, stationary upright cycle ergometer. Each session will begin with 5 min of cycling at 15% of the peak power output (*W*peak) recorded during the baseline cardiopulmonary exercise test. The main body of each session will involve ten 1-min bouts of cycling at 90% of *W*peak, interspersed with 1-min bouts of cycling at 15% of *W*peak [11]. The session will end with 3 min of cycling at 15% of *W*peak. Similar protocols of HIIT have been shown to be safe and effective for improving cardiorespiratory fitness in various clinical and non-clinical populations [12, 13]. Incremental cycle exercise testing, without the analysis of expired gases and blood lactate responses, will be performed during the final sessions of the fourth and eighth week of training (i.e. at sessions 12 and 24 of 36) and will replace the normal exercise training of those sessions. The peak power output recorded during these tests will be used to adjust the power output used within the training sessions (i.e. the training will be progressed after 4 and 8 weeks according to changes in peak power output assessed using incremental cycle exercise testing).

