### Statistical analysis

A detailed analysis plan will be prepared and agreed with the Trial Management Group and Trial Steering Committee, before all of the data has been collected. Analyses will be conducted in STATA (StataCorp, 2013) using the principles of intention-to-treat. The flow of participants through each stage of the trial will be presented in a CONSORT diagram. Descriptive statistics will be used to characterise the groups at baseline and to present the feasibility outcomes. Although determining differences in clinical outcomes between the three arms is not the primary purpose of this trial, comparisons will be undertaken to investigate the feasibility of studying these outcomes and to calculate estimates for the likely effect sizes and 95% confidence intervals. As recommended in guidelines for good practice for the analysis of pilot studies [23], the focus of the results will be on the estimates of the treatment effects rather than statistical significance and as such no hypothesis testing will be undertaken. Differences between the two comparison groups will be presented in the form of an unadjusted mean difference for continuous outcomes, and an odds ratio for binary outcomes, with their associated 95% confidence intervals.

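### Oxygen uptake is specified only in mL/kg/min and compared unadjusted, so weight change enters the fitness estimate; an adjusted L/min analysis beside it would separate the two at no data cost.

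*Protocol article*

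**What the plan says.** Under Behavioural and health-related outcomes, the protocol article defines the fitness outcomes: "The assessment of cardiorespiratory fitness will be achieved by measuring ventilatory threshold and peak oxygen uptake". It then fixes the unit: "Oxygen consumption will be expressed relative to body mass", given as mL/kg/min. No absolute unit is named anywhere in the article, and none is ruled out.

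The same section lists the physical measures taken "before randomisation and 13 weeks after randomisation: body mass, stature, waist circumference, blood pressure", with fitness in the same list. Body mass is therefore an outcome in its own right at the two visits where fitness is tested.

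Under Statistical analysis, group differences are to be presented as an "unadjusted mean difference for continuous outcomes" with a 95% confidence interval, and "no hypothesis testing will be undertaken". No adjustment for baseline fitness or body mass is stated. A separate, more detailed analysis plan is announced there but is not available for this review.

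The third objective, at the end of the Background, is to choose a primary outcome and obtain the parameters for sizing the full trial.

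**The concern.** Peak oxygen uptake in mL/kg/min is a ratio whose denominator is measured after randomisation. Body mass can change with training or with the course of Crohn's disease. When mass falls, the ratio rises relative to the absolute uptake; when mass rises, it falls. An unadjusted comparison of means cannot tell a change in aerobic capacity from a change in weight.

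The test is done on a cycle ergometer with the load set in watts, so nothing in the test requires division by mass. Training itself is prescribed from an absolute quantity, the "peak power output (*W*peak) recorded during the baseline cardiopulmonary exercise test".

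What is at stake is the planning information. If fitness is considered as the full trial's primary outcome, the effect estimate and SD carried forward will combine fitness with weight change, in proportions that the reader cannot see from that figure alone.

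**Working it through.** **The plan's own figure.** The Sample size section aims for 12 participants per arm with full data and allows 20% attrition: 12 / (1 − 0.20) = 15 per arm, and 3 × 15 = 45. This reproduces the stated total. The present point does not depend on it, except that 12 per arm is used below.

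**Inputs from the article.** Unit: mL/kg/min. Body mass: measured at baseline and week 13. Comparison: unadjusted mean difference. Completers: 12 per arm.

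**Assumptions.** The article gives no baseline uptake, SD, expected weight change or expected change in uptake, so ranges are used. The ratio is taken to use body mass at the visit of the test. The ventilatory threshold is taken to be expressed as oxygen uptake at the threshold.

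**Formula.** Relative uptake = absolute uptake / mass. If mass falls by a fraction w and absolute uptake by a fraction f, the reported change is (1 − f)/(1 − w) − 1.

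**Absolute uptake unchanged (f = 0):** the reported change is 1/(1 − w) − 1.

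| Loss of mass | Reported change |
|---|---|
| 1% | +1.0% |
| 3% | +3.1% |
| 5% | +5.3% |
| 8% | +8.7% |
| 10% | +11.1% |

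For a 5% loss this is +1.3, +1.6 or +1.8 mL/kg/min at an assumed baseline of 25, 30 or 35.

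**Absolute uptake also falls, with a 5% loss of mass:**

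| True change in uptake | Reported change |
|---|---|
| −3% | 0.97/0.95 − 1 = +2.1% |
| −5% | 0.95/0.95 − 1 = 0% |
| −10% | 0.90/0.95 − 1 = −5.3% |

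So there are three cases. If f is less than w, the ratio shows a false gain. If f equals w, it shows no change. If f exceeds w, it shows a decline smaller than the true one.

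**Absolute uptake rises, with a 5% loss of mass:** true gains of 5%, 10% and 15% are reported as 1.05/0.95 − 1 = 10.5%, 1.10/0.95 − 1 = 15.8% and 1.15/0.95 − 1 = 21.1%.

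**Effect on an arm mean.** Take a baseline of 30 mL/kg/min, unchanged absolute uptake, and k of 12 completers each losing 5% of mass. The shift is (k/12) × 30 × (1/0.95 − 1):

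- k = 1: 0.13 mL/kg/min
- k = 3: 0.39 mL/kg/min
- k = 12: 1.58 mL/kg/min

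The between-arm difference moves only by the part of this shift that the arms do not share.

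**Imprecision for comparison.** With 12 per arm, the 95% half-width is t(0.975, 22 df) × SD × √(2/12). It is 3.4, 5.1 or 6.8 mL/kg/min for an assumed SD of 4, 6 or 8.

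**The case against.** The case on the other side is substantial, and much of it stands.

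- **The unit is conventional and not exclusive.** The article states one unit without excluding others, and the unseen analysis plan may add absolute values or covariates. That stands: this is neither an error nor a contradiction. What remains is that the unit and the unadjusted comparison are both written down, and together they let weight change into the estimate.
- **A reader might infer that a participant who relapses and loses weight will be scored as fitter.** The article does not support that as a general statement. It holds only if absolute uptake falls by a smaller fraction than mass, and no figure is given for either change. Likewise, a participant who gains lean mass is scored as less fit only if uptake fails to rise in proportion.
- **A reader might infer that the decision to proceed is affected.** It is not. Criteria for success uses fitness only for completeness: at least 67% of participants must supply valid fitness, CDAI and IBDQ data at week 13. The test-validity criteria (respiratory exchange ratio, perceived exertion, heart rate and lactate) do not involve body mass. Nor does the article name fitness as the intended primary outcome; it is one of several that could be chosen.
- **The information is not lost.** Body mass is recorded at the same visits, so absolute uptake can be recovered. Relapse is captured separately: "Relapse will be defined as an increase in CDAI score of at least 100 points, to a level greater than 150". Both are true, but neither corrects the fitness mean unless someone does the analysis.
- **The arm-level shift is small beside the imprecision.** It is, in the scenarios above. But imprecision is not a reason to leave an avoidable systematic component in a planning estimate.
- **Making L/min the deciding result would be a preference with its own cost.** This also stands. Unadjusted L/min carries differences in body size between participants into a comparison of about 12 per arm and into its SD. For that reason L/min belongs beside mL/kg/min, with adjustment, and not in its place.

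**Conclusion.** The point holds as a minor, free improvement. The article names a single unit for oxygen uptake, divides by a quantity that is itself a week-13 outcome, and compares arms without adjustment. The size for an individual follows from arithmetic alone: a 5% loss of mass adds 5.3% when absolute uptake is unchanged, and it turns a true 5% fall into no reported change. At arm level, under the assumed baseline of 30 mL/kg/min and 5% losses, the shift is 0.13 to 0.39 mL/kg/min if one to three of 12 lose weight, and 1.58 if all do. The corresponding confidence-interval half-width is 3.4 to 6.8.

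All values for baseline, SD, weight change and change in uptake are assumptions. The point also assumes that the ratio uses body mass at each visit. The sample size and the success criteria are unaffected, and no hypothesis test is planned. The consequence is confined to the effect estimate and SD that the third objective would carry into the full trial.

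**What to change.** In Behavioural and health-related outcomes, state that peak oxygen uptake and oxygen uptake at the ventilatory threshold will be analysed in L/min as well as in mL/kg/min, and that the ratio uses body mass measured at the same visit.

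In Statistical analysis, add that the between-arm difference in L/min will be estimated with adjustment for the baseline value of the outcome and baseline body mass, with a 95% confidence interval. Both covariates precede randomisation. Week-13 body mass should not be used as a covariate, because it may itself be affected by allocation. Present this result beside the mL/kg/min result and the change in body mass by arm. Use both when choosing the primary outcome and the SD for the full trial, and record which analysis each SD comes from. Neither unit needs to be declared decisive.

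The cost is wording and a small amount of analysis. No visit, test, sample or participant is added, since gas exchange and body mass are already collected. The adjusted L/min estimate is an addition to the unadjusted comparison already stated. In a two-arm comparison of 24 completers it uses two further degrees of freedom (24 − 4 = 20 instead of 24 − 2 = 22).

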### Participant timeline

Figure 1 illustrates the process of enrolling participants into the study, the interventions being compared, and timing of assessments and hospital visits for the participants in the trial.

**Fig. 1 Fig1:**
[figure not shown]
Schematic diagram of recruitment and assessment

### Sample size

As this is a feasibility study, no formal sample size calculation was performed [26]. Instead, this study follows sample size recommendations for pilot randomised controlled trials [27] and aims to have at least 12 participants per study arm who provide full data. We aim to recruit 15 participants to each group (i.e. total sample size of 45) to allow up to 20% attrition, which is appropriate based on our exercise studies in other clinical populations [28–30]. This number of participants is deemed adequate to provide sufficient information on key feasibility issues such as recruitment, retention and acceptability of the exercise programmes.

### Recruitment

Recruitment methods will include advertisements through the local media and charity groups (e.g. Crohn’s and Colitis UK), invitations to participants in previous studies who have given their consent to be contacted regarding future research projects, and liaisons with direct care teams at recruiting NHS Hospital Trusts. For the latter of these methods, a member of the direct care team will identify potentially eligible patients via review of medical notes ahead of clinics and database screening of clinic letters.

Potentially eligible patients will be screened for participation in the study by a member of the direct care team with eligibility confirmed by a delegated clinical co-investigator. Data used for calculating the CDAI and faecal calprotectin results must have been collected no greater than 4 weeks before the screening visit. Once an eligible patient has consented to study participation (consent being obtained in writing by a research nurse), their contact details will be forwarded to the research assistant, who will contact the participant to book them in for their baseline assessment, which must be performed within 4 weeks from when the screening assessments have been fully completed.

### Randomisation and allocation concealment

Following collection of all baseline measurements, participants will be randomly assigned 1:1:1 to HIIT, MICT or usual care control. Randomisation will be achieved using a computer-generated randomisation schedule stratified by centre and baseline disease status (inactive [CDAI <150] vs. mildly active [CDAI 150–219]) using permuted blocks of random sizes. The block sizes and allocation sequence will not be disclosed to ensure concealment. A statistician at York Trials Unit will manage the randomisation process. The intervention facilitator (research assistant) will request email notification of a participant’s treatment allocation after baseline assessments have been completed. They will then inform the participant of their allocation (i.e. participants will not be blinded to the treatment allocation).

### Blinding

Blinding of trial participants and the intervention facilitator is not possible. Questionnaires will be completed by the participants independently and checked by a researcher for completeness. Anthropometric, cardiorespiratory fitness and disease activity outcomes will be assessed by researchers blinded to group allocation. Participants will be asked not to disclose their allocation to the technician.

### Statistical analysis

A detailed analysis plan will be prepared and agreed with the Trial Management Group and Trial Steering Committee, before all of the data has been collected. Analyses will be conducted in STATA (StataCorp, 2013) using the principles of intention-to-treat. The flow of participants through each stage of the trial will be presented in a CONSORT diagram. Descriptive statistics will be used to characterise the groups at baseline and to present the feasibility outcomes. Although determining differences in clinical outcomes between the three arms is not the primary purpose of this trial, comparisons will be undertaken to investigate the feasibility of studying these outcomes and to calculate estimates for the likely effect sizes and 95% confidence intervals. As recommended in guidelines for good practice for the analysis of pilot studies [23], the focus of the results will be on the estimates of the treatment effects rather than statistical significance and as such no hypothesis testing will be undertaken. Differences between the two comparison groups will be presented in the form of an unadjusted mean difference for continuous outcomes, and an odds ratio for binary outcomes, with their associated 95% confidence intervals.

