**Methods:**

This is a randomised, controlled, assessor-blinded, feasibility trial with three parallel groups. Forty-five adults with inactive or mildly active Crohn’s disease will be randomly assigned 1:1:1 to HIIT, MICT or usual care control. Participants in the HIIT and MICT groups will be invited to undertake three sessions of supervised exercise each week for 12 consecutive weeks. HIIT sessions will consist of ten 1-min intervals of cycling exercise at 90% of peak power output separated by 1 min of active recovery. MICT sessions will involve 30 min of continuous cycling at 35% of peak power output. Participants will be assessed before randomisation and 13 and 26 weeks after randomisation. Feasibility outcomes include rates of recruitment, retention and adherence. Interviews with participants will explore the acceptability of the exercise programmes and study procedures. Clinical/health outcomes include cardiorespiratory fitness, body mass index, resting blood pressure, markers of disease activity (faecal calprotectin and Crohn’s Disease Activity Index) and activated T cell cytokine profiles. Study questionnaires include the Inflammatory Bowel Disease Quality of Life Questionnaire, EQ-5D-5L, IBD Fatigue Scale, Hospital and Anxiety Depression Scale, and International Physical Activity Questionnaire.

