We hypothesise that supervised exercise training will be an effective means of improving health-related quality of life, fatigue and physical and mental health in people with inactive or mildly active CD. Before embarking on an adequately powered randomised controlled trial to test this hypothesis, we have planned a feasibility study that will address several areas of uncertainty. For example, fatigue and a perceived inability to manage exercise have been cited as barriers to exercise in people with inflammatory bowel disease [9]. This raises questions about how easy it will be to recruit and retain participants in a supervised exercise training trial. The objectives of the present feasibility study are the following:To explore the acceptability, safety and potential benefits of HIIT and MICT in people with inactive and mildly active CD, relative to usual care.To evaluate the feasibility of conducting a future large-scale randomised controlled trial to assess the clinical effectiveness of exercise training in people with CD in terms of recruitment, retention, adherence and acceptability.To identify a primary outcome and estimate the parameters required to inform sample size calculation for an adequately powered randomised controlled trial.

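### The protocol fixes treatment effects as unadjusted differences between two unnamed groups in a three-arm trial that collects baseline values, which costs precision if baseline and follow-up are moderately correlated

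*Protocol article*

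**What the plan says.** The Statistical analysis section puts the emphasis on estimated treatment effects with 95% confidence intervals and rules out hypothesis tests. It speaks of comparing clinical outcomes across three arms, and then defines the estimate: "Differences between the two comparison groups will be presented in the form of an unadjusted mean difference for continuous outcomes". Binary outcomes get an odds ratio. A detailed analysis plan is to follow.

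Other sections bear on that sentence:

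- **Design.** The abstract states: "This is a randomised, controlled, assessor-blinded, feasibility trial with three parallel groups". The randomisation section agrees: "participants will be randomly assigned 1:1:1 to HIIT, MICT or usual care control". The first objective sets HIIT and MICT each relative to usual care.
- **Baseline data.** Under Behavioural and health-related outcomes: "we will assess the following outcome measures in all participants before randomisation and 13 weeks after randomisation". The questionnaires are also given before randomisation.
- **Stratification.** Allocation is "stratified by centre and baseline disease status".
- **Purpose.** The third objective is: "To identify a primary outcome and estimate the parameters required to inform sample size calculation".
- **Size.** The trial "aims to have at least 12 participants per study arm who provide full data".

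**The concern.** There are two separate difficulties.

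First, the definition of the estimate refers to two groups where there are three, and nothing says which two. Each programme against usual care, HIIT against MICT, and pooled exercise against usual care are all possible.

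Second, the word unadjusted is a stated choice, not a detail left open. An analysis plan that follows the protocol inherits it, and one that adjusts departs from it. With about 12 participants per arm, baseline means can differ noticeably by chance. An unadjusted follow-up difference carries r times that gap into the estimate.

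At stake is the quality of the effect estimates that the trial says are its focus. So is the usefulness of the sample-size parameters: a main trial analysed with baseline adjustment needs r or the residual SD as well as the raw SD.

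**Working it through.** **Inputs from the protocol.** Three arms, 1:1:1; 12 per arm with full data; 15 per arm recruited; attrition up to 20%; 95% intervals; three hospital trusts, taken here as three centres (2 df); disease status in two categories (1 df).

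**Assumed input.** r, the correlation between baseline and follow-up, which the protocol does not give. Results are in units of the outcome SD.

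**Step 1: the protocol's own figure.** 12 / (1 − 0.20) = 15 per arm, and 15 × 3 = 45. This reproduces "We aim to recruit 15 participants to each group (i.e. total sample size of 45) to allow up to 20% attrition" and is not in dispute.

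**Step 2: chance imbalance at 12 per arm.** The SE of a difference in baseline means is √(2/12) = 0.408 SD. The probability of a gap above 0.5 SD is 2 × [1 − Φ(0.5/0.408)] = 0.22 for a given pair of arms, and about 0.44 by simulation for at least one of the three pairs. A 0.5 SD gap at r = 0.7 moves the unadjusted difference by 0.7 × 0.5 = 0.35 SD.

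**Step 3: unadjusted half-width.** Three-arm model, 36 − 3 = 33 residual df: t(0.975, 33) × √(2/12) = 2.0345 × 0.4082 = 0.831 SD. A separate two-arm analysis with 22 df gives 0.847 SD. The 0.831 figure is the right comparator for an adjusted three-arm model.

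**Step 4: adjusted half-width.** With p covariates the expected half-width is about t(0.975, 33 − p) × √[(2/12)(1 − r²)(1 + p/(32 − p))].

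- Baseline only, p = 1: t(0.975, 32) = 2.0369, and the last factor is 1 + 1/31.
- Baseline, centre and disease status, p = 4: t(0.975, 29) = 2.0452, and the last factor is 1 + 4/28. Centre and disease status are assumed to have no prognostic value, which is the unfavourable case for adjusting.

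| r (assumed) | Unadjusted | Baseline only (ratio) | Baseline + centre + status (ratio) |
|---|---|---|---|
| 0 | 0.831 | 0.845 (1.02) | 0.893 (1.07) |
| 0.3 | 0.831 | 0.806 (0.97) | 0.852 (1.03) |
| 0.5 | 0.831 | 0.732 (0.88) | 0.773 (0.93) |
| 0.7 | 0.831 | 0.603 (0.73) | 0.637 (0.77) |
| 0.85 | 0.831 | 0.445 (0.54) | 0.470 (0.57) |

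Simulation with 2,000 runs per setting gave ratios of 0.97, 0.88 and 0.73 (baseline only) and 1.02, 0.93 and 0.76 (all covariates) at r = 0.3, 0.5 and 0.7, in line with the formula.

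**Step 5: break-even.** Equating each adjusted half-width with 0.831 gives r of about 0.2 for baseline only and about 0.37 with all four covariate df.

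**Step 6: the low end of recruitment.** The success criteria accept 24 recruits, or 8 per arm before attrition. The unadjusted three-arm half-width is then 1.04 SD. At r = 0.5, baseline only gives 0.93 SD and the four-df model 1.02 SD, so the stratification terms use up most of the gain.

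**The case against.** The case for leaving the sentence alone has real substance.

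- **Validity.** A reader might infer that the planned estimates are biased or the intervals wrong. The design does not support that. Randomisation makes the unadjusted difference unbiased. Omitting a stratification factor makes the interval conservative if the factor is prognostic and leaves coverage unaffected if it is not.
- **Precision.** A reader might also call this the least precise analysis available. It is not: a difference in change scores has variance proportional to 2(1 − r) and is less precise whenever r < 0.5. Adjustment itself loses a little when r is near zero. Low r is plausible for some outcomes, because eligibility caps CDAI at 219 and requires faecal calprotectin below 250 mcg/g, and such truncation weakens correlation.
- **Design parameters.** The raw SD is a valid input for a main trial and converts to a residual SD once r is known. Nothing in the protocol forbids reporting r.
- **Scope.** Not every measure has a baseline. The enjoyment scale is given only at week 13 and only in the exercise arms, and session adherence has none.
- **Consequence.** There are no hypothesis tests, and the success criteria rest on acceptability, recruitment and data completeness.
- **Wording.** Pairwise comparison with usual care is the natural reading of the two groups, and the pending analysis plan could say so and add adjusted estimates.

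All of this limits the size of the point. It does not remove it: the protocol names the unadjusted estimator, leaves the contrasts unstated, and gives no reason for setting aside baseline values that it collects.

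**Conclusion.** The point holds as a modest recommendation about precision and clarity. With 12 per arm and a three-arm model, adjusting for baseline alone narrows the interval by about 12% at r = 0.5, 27% at r = 0.7 and 46% at r = 0.85. With centre and disease status added and non-prognostic, the gains are about 7%, 23% and 43%. Below r of about 0.2 or 0.37 respectively there is no gain. These figures rest on assumed correlations, a linear relation with common variance, and the target of 12 complete participants per arm. They concern continuous outcomes with a baseline value and do not carry over to the odds ratios. Type I error, power and the decision to proceed to a full trial are untouched.

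**What to change.** Replace the sentence with wording such as: *For each continuous outcome measured at baseline, one linear model across the three arms, adjusted for the baseline value of that outcome (and for centre and baseline disease status where numbers allow), gives HIIT vs usual care, MICT vs usual care and HIIT vs MICT with 95% CIs. The unadjusted difference, the raw and residual SD and the baseline-follow-up correlation are reported alongside for the design of the main trial.*

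The cost is a change of wording and a few lines of code, with no extra data collection. The statistical price is one to four degrees of freedom and an interval about 2% to 7% wider for outcomes where r is near zero. If recruitment ends near 24, adjusting for baseline alone is the safer form. The article reports recruitment as ongoing and the detailed analysis plan as still to be prepared, so on its account the change can be made before the data are complete.
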